### Randomization and blinding

Following baseline measurements, subjects will be randomly allocated to one of two treatment groups, ie., tens or sham tens. However, all patients will be told that two different kinds of tens are being tested. Randomization will be performed in blocks of four, stratified by sex and age. The allocation of this will be done by an independent researcher who will not interfere with other experimental procedures. We will use two boxes: one for each sex. In each box, subgroups will be made for five age categories: 50-59; 60-69; 70-79; 80-89; 90-99 years. Four numbered cards will be put in each age category. The numbering of the cards starts at one and ends at 40 and each number will correspond to a tens or a sham tens treatment. At the start of the study, each age category contains two tens and two sham tens treatments. Each time a new patient is included, a card will be taken out of the corresponding box and age category. When the four cards of one category are used, all of them will be put back in the box, so that a second round can be started. At each round, the numbered cards will be differently assigned to a tens/sham tens treatment by an independent researcher. The measurements will be carried out by a different researcher than the one that informs the patients concerning the treatment modalities. The information of the baseline measurements will remain concealed until the end of the study ensuring blinded assessment.

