### Sample size

Sample size calculation is based on data from Law and Cheing [30]. They found a significant difference in the reduction of pain (2.9(4.7) points on a 0-10 VAS) when applying a tens current (pulse width: 200 μs, frequency: 100 Hz) on the knee of patients with OAk compared to a control group not receiving tens treatment. In this study the response within each subject group was normally distributed with standard deviation 4.7. If the true difference in the experimental and control means is 2.9, we will need to study 42 experimental subjects and 42 control subjects to be able to reject the null hypothesis that the population means of the experimental and control groups are equal with probability (power) 0.8. The Type I error probability associated with this test of this null hypothesis is 0.05. To take into account a 15% loss of data sample size is inflated up to 50 per group (n/0.85). Sample size is augmented by 10% per potential confounding factor (i.e. age and sex) [31]. The total sample size to be recruited will be 120 subjects.

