### Outcome assessment

#### Primary outcome variable

The change from baseline to final assessment of the study knee in the continuous variables *"overall average knee pain" (KPa) and "peak pain over the last 24 h" (KPp*) will be measured using a numeric rating scale [32].

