### Data reduction and Statistical analysis

An intention-to-treat analysis will be performed so that the integrity of the randomization is ensured. Normality will be checked via the Shapiro-Wilk test.

To ensure good balance of participant characteristics in each group at baseline, stratification is used [39]. Changes in differences between both treatment groups after the intervention period (at 6 w and 12 w) will be analyzed using repeated measures ANOVA for the following variables: KPp, KPa, WOMAC subscores for pain and function, GPE. If the modulus of the partial correlation of potential confounding factors age and sex with the primary outcome values equals minimum 0.3, these covariates of prognostic values will be added as covariates in the ANOVA model [40].

As a secondary analysis, a linear regression analysis will be used with the following dependent factors: BMI, TS and DNIC; and as independent factors: KPa, KPp, WOMAC subscales for pain and function.

Significance value for all tests will be set at p < 0.05. All analyses will be performed using SPSS 20 for Windows.

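### Age and sex, the randomization strata, enter the primary model only if an observed correlation reaches 0.3, and baseline pain is not a covariate; the model hangs on trial outcomes and precision is lost, though type I error is not inflated

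*Protocol article*

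**What the plan says.** All references are to the Protocol article.

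- **Randomization and blinding:** "Randomization will be performed in blocks of four, stratified by sex and age". There are two sexes and five age bands, so ten strata.
- **Sample size:** "Sample size is augmented by 10% per potential confounding factor (i.e. age and sex"), which takes the total from 100 to 120.
- **Primary outcome variable:** two primary outcomes, KPa and KPp, each defined as "The change from baseline to final assessment of the study knee in the continuous variables" named there.
- **Data reduction and Statistical analysis:** the 6- and 12-week results "will be analyzed using repeated measures ANOVA for the following variables: KPp, KPa, WOMAC subscores for pain and function, GPE". Age and sex are conditional: "If the modulus of the partial correlation of potential confounding factors age and sex with the primary outcome values equals minimum 0.3". When a factor meets that condition it enters the model; otherwise the analysis is not adjusted for it. They are the only candidate covariates. Baseline pain enters through the change from baseline or as one level of the repeated measure, not as a covariate.
- **Knee pain and physical function (baseline measurements):** KPa, KPp and WOMAC are all collected at baseline.

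**The concern.** Balancing the arms on age and sex by design makes the treatment estimate more stable wherever those factors predict pain. The analysis reflects that stability only if it includes them. Here inclusion is decided by a correlation computed from the trial's own outcomes, so a moderately prognostic factor may be in or out of the model by chance. The text does not say whether the correlation is taken with KPa, with KPp or with each, so the two primary outcomes could end up with different covariates.

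Separately, baseline pain is measured on the same scale as the outcome but is not used as a covariate. A raw change score subtracts the whole baseline value whatever its correlation with follow-up, and this is less efficient than regressing on it. At stake are a determinate primary model and its precision, not the validity of the comparison.

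**Working it through.** **1. The plan's own figure.** Inputs from the Sample size section: difference 2.9 ("If the true difference in the experimental and control means is 2.9, we will need to study 42 experimental subjects and 42 control subjects"); SD 4.7 ("the response within each subject group was normally distributed with standard deviation 4.7"); power 0.80; type I error 0.05. Sidedness is not stated; two-sided reproduces the figure, one-sided gives 33.

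n per group = 2 × [4.7 × (1.960 + 0.842) / 2.9]² = 41.2, so 42. Loss: 42 / 0.85 = 49.4, so 50. Two factors: 100 × 1.2 = 120. The stated 42, 50 and 120 all reproduce. Evaluable after 15% loss: 120 × 0.85 = 102, or 51 per group.

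**2. How often the 0.3 rule selects a factor.** Fisher's transformation with one other variable partialled out (an assumption): SE = 1/√(102 − 3 − 1) = 0.101, and the cut-off is atanh(0.3) = 0.310. For a true correlation of 0.2, atanh(0.2) = 0.203 and (0.310 − 0.203)/0.101 = 1.06, giving a selection probability of about 15%.

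| True partial correlation | 0.2 | 0.25 | 0.3 | 0.35 | 0.4 |
|---|---|---|---|---|---|
| Probability of selection | 15% | 30% | 50% | 71% | 87% |

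**3. What omitting the strata costs.** Omitting a factor with correlation r multiplies the residual variance by 1/(1 − r²). At r = 0.3 that is 1/0.91 = 1.10. For two uncorrelated factors at 0.3 it is 1/(1 − 0.18) = 1.22. These are ceilings for factors just under the cut-off.

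A simulation puts this into operating characteristics: 102 subjects, blocks of four within sex-by-age strata, 6,000 runs per scenario, age and sex distributions assumed, effect 2.9/4.7 = 0.617 SD. The Monte Carlo standard error near 5% is √(0.05 × 0.95/6000) = 0.28 percentage points.

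| True r, age and sex each | Type I error: never / rule / always adjusted | Power: never / rule / always adjusted |
|---|---|---|
| 0.20 | 4.0 / 4.3 / 4.6% | 88.2 / 88.9 / 89.7% |
| 0.28 | 3.2 / 4.5 / 4.9% | 88.7 / 90.9 / 92.0% |
| 0.30 | 3.1 / 4.6 / 4.9% | 88.6 / 91.1 / 92.1% |

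The never-adjusted analysis is conservative. The rule recovers most of the calibration and falls about one power point short of always adjusting.

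**4. What not adjusting for baseline pain costs.** For one follow-up visit, with equal variance σ² at baseline and follow-up and correlation ρ (not in the document, so assumed), the change score has variance 2(1 − ρ)σ² and ANCOVA has residual variance (1 − ρ²)σ². Their ratio, ANCOVA to change, is (1 + ρ)/2, so the reduction is (1 − ρ)/2. The power column takes 4.7 as the SD of change and 51 per group. Unadjusted power is then Φ(2.9/[4.7 × √(2/51)] − 1.960) = Φ(1.156) = 87.6%.

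| ρ | Change score | ANCOVA | Reduction | n per group for 80% power | Power at 51 per group |
|---|---|---|---|---|---|
| 0.3 | 1.40 | 0.91 | 35% | 27 | 97.2% |
| 0.5 | 1.00 | 0.75 | 25% | 31 | 94.9% |
| 0.7 | 0.60 | 0.51 | 15% | 36 | 92.2% |
| 0.8 | 0.40 | 0.36 | 10% | 38 | 90.7% |

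If the ANOVA instead compared follow-up values alone, its variance would be 1.10, 1.33, 1.96 or 2.78 times that of ANCOVA at the same four values of ρ.

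**The case against.** The strongest case for the plan is that the rule is an algorithm fixed in advance: candidates, statistic, cut-off and action are all stated. It tends to admit a factor that matters, does not inflate type I error, and costs about one power point. Change from baseline is the declared endpoint, and its unadjusted contrast is valid under randomization. ANCOVA is therefore a gain in efficiency, not the repair of a bias, and that gain rests on assumed correlations and shrinks as ρ rises. All of this stands, and it limits the point to precision and determinacy.

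A reader might infer four stronger things that the documents do not support.

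- *The primary analysis is not pre-specified.* The selection rule is pre-specified; only the resulting model is not known in advance.
- *The 20% enlargement is thrown away, or contradicts the conditional rule.* The extra subjects are analysed whether or not covariates enter. Both sections call age and sex potential confounders, so allowing sample size for a possible adjustment is compatible with a conditional one.
- *The model may differ between visits.* The text describes one repeated measures ANOVA covering 6 and 12 weeks and says nothing of choosing covariates by visit. A difference between KPa and KPp is possible, because the text does not settle which of them drives the rule.
- *Baseline pain is ignored.* It is used through the change from baseline; it is just not a covariate.

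An unshown analysis plan might add a baseline covariate. The threshold, however, is stated in this document, and age and sex are the only covariates it names.

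**Conclusion.** The point holds as one of determinacy and efficiency. Whether the stratification factors enter the primary model depends on trial outcomes, with about an even chance of inclusion at a true correlation of 0.3 and 102 evaluable subjects. When they stay out, the standard error is somewhat too large, which is conservative. The rule's own cost is about one power point for assumed correlations of 0.2 to 0.3 each and assumed age and sex distributions.

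The larger loss comes from baseline pain: 35% to 10% of the variance of the treatment effect against a change-score analysis, for assumed ρ from 0.3 to 0.8 with equal variances at baseline and follow-up. The power figures also assume that 4.7 is the SD of change. Nothing here makes the planned comparison invalid, and on the protocol's own inputs unadjusted power at 51 per group is already above the 80% target. The change is still worth making because it is nearly free and leaves one determinate model that matches the design.

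**What to change.** Delete the 0.3 rule. In the models for KPa, KPp and each WOMAC subscore, always include as covariates:

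- sex;
- age in one form stated now, either the randomization age category with the sparse oldest categories merged by a stated rule, or linear age;
- the baseline value of the outcome being analysed.

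State that only the 6- and 12-week values are repeated measures, so that baseline is not both a covariate and a level of the time factor. GPE has no baseline value, so the baseline term does not apply to it.

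All these variables are already collected at baseline. The cost is wording and a few degrees of freedom; sample size, visits and procedures do not change.

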### Aim of the proposed study

This study has a double aim. First to explore the pain inhibitory effect of burst tens in OAk patients. Second, to assess whether central sensitization affects this pain inhibitory effect. A 6 week burst tens intervention period will be succeeded by a 12 week follow up period. As an international consensus definition for central sensitization is lacking [26], we aim to assess the central sensitization by measuring pressure pain thresholds (PPT) at the knee (local pain) and at the upper limb (spreading pain) [27] and temporal summation before and during a heterotopic noxious conditioning stimulation [16,21]. The test-retest reliability of TS and DNIC has been reported as acceptable [21].

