#### Central sensitization

Temporal summation as well as diffuse noxious inhibitory control will be used to detect central sensitization. The assessment will be done in accordance with the protocol of Cathcart et al. [21]. The outcome assessor will be trained by an experienced researcher prior to the start of the study. The intra-observer reliability of the outcome assessor will be tested in a subgroup of the participants.

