#### Pressure pain threshold (PPT)

Pressure stimuli will be measured using a hand held digital algometer (Somedic AB, Farsta, Sweden). Pain detection thresholds will be measured on the knee (M. Vastus Medialis) and on the upper part of the homolateral arm (lateral part of M. Deltoideus, 10 cm below acromion) [33]. The pressure will be increased at a rate of approximately 1 kg/s. Subjects have to report when the feeling of pressure alone changes into a feeling of pressure and pain (Pain Detection Threshold). The mean of two measurements, taken 30 s apart from each other, will be used for further use (temporal summation).

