#### Temporal summation (TS)

Temporal summation assessment will start 2 min after PPT measurements to avoid contamination by possible sensitization from the pain threshold stimulation. TS will be induced at the knee and arm through 10 pressure pulses with the hand held algometer (Somedic AB, Farsta, Sweden) at PPT intensity. For each pulse, pressure will be increased at a rate of 2 kg/s and held during 1 s. An interstimulus interval of 1 s will be applied. Patients will be instructed to rate their pain level according to a NRS at the first, 5th and 10th pulse [21].

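### The markers for the second aim are listed inconsistently: pressure pain thresholds count as a measure of central sensitization in the aim, but enter no listed analysis

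*Protocol article*

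**What the plan says.** The second aim is given in the protocol article, *Aim of the proposed study*: "Second, to assess whether central sensitization affects this pain inhibitory effect". The same section notes that no consensus definition exists and then lists the measures: "we aim to assess the central sensitization by measuring pressure pain thresholds (PPT) at the knee (local pain) and at the upper limb (spreading pain"), together with "temporal summation before and during a heterotopic noxious conditioning stimulation".

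The later sections differ:

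- *Central sensitization* (under Baseline measurements): "Temporal summation as well as diffuse noxious inhibitory control will be used to detect central sensitization". PPT is not named.
- *Pressure pain threshold (PPT)*: "Pain detection thresholds will be measured on the knee (M. Vastus Medialis) and on the upper part of the homolateral arm". The only use given is that the mean of two readings "will be used for further use (temporal summation").
- *Temporal summation (TS)*: the stimulus is "10 pressure pulses with the hand held algometer (Somedic AB, Farsta, Sweden) at PPT intensity". The DNIC section repeats this TS assessment while the opposite arm is compressed.
- *Secondary outcome variables*: PPT stands beside TS and DNIC as a baseline variable. *Follow up* repeats all three at 6 and 12 weeks.
- *Data reduction and Statistical analysis*: "a linear regression analysis will be used with the following dependent factors: BMI, TS and DNIC", with the two pain ratings and the WOMAC pain and function subscales on the other side. The repeated measures ANOVA covers the pain ratings, the WOMAC subscores and global perceived effect.
- *Discussion*: the second aim is restated in terms of TS and DNIC.

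**The concern.** A reader cannot tell which markers answer the second aim. By the aim section, a patient with a low arm threshold and little summation shows one of the named signs of central sensitization. By the measurement and analysis sections, the same patient shows none. The Discussion wants to identify non-sensitized patients who are likely to benefit from burst TENS, and membership of that group depends on which section is followed.

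Two things are at stake. A conclusion about central sensitization in general could be drawn although one component named in the aim was never examined. And if the text is left as it is, the choice of markers can be made after the results are known.

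This is not simply a detail left out of a condensed article. The regression variables are listed by name. The list includes BMI, which the aim does not name as a measure of sensitization, and leaves out PPT, which the aim does name.

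**Working it through.** No figure in the plan depends on this point, so the check sets the sections side by side.

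| Section of the protocol article | PPT | TS | DNIC |
|---|---|---|---|
| Aim of the proposed study | yes, knee and arm | yes | yes (TS during conditioning) |
| Central sensitization (measurement) | no | yes | yes |
| Pressure pain threshold | only to set the TS stimulus | – | – |
| Secondary outcome variables | baseline variable | baseline variable | baseline variable |
| Follow up, 6 and 12 weeks | measured | measured | measured |
| Statistical analysis, ANOVA | no | no | no |
| Statistical analysis, regression | no | yes | yes |
| Discussion, second aim | no | yes | yes |

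**Step 1. Is PPT analysed anywhere?** It is collected at 2 sites on 3 occasions (baseline, 6 and 12 weeks), so 6 site-by-visit values per patient. It is in neither variable list of the analysis section.

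**Step 2. Could TS and DNIC carry the same information?** Not directly. The TS pulses are given at the patient's own PPT, and the DNIC test repeats TS in the same way. A patient with a low threshold gets a weaker pressure and a patient with a high threshold a stronger one, so the ratings describe the response relative to the threshold and not the threshold itself. How strongly PPT correlates with TS or DNIC is not stated, so the loss cannot be put in numbers from the documents.

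**Step 3. Would adding PPT to the regression as worded be enough?** No. The sentence makes the markers the dependent variables and the pain scores the independent ones. It names no treatment term and no arm-by-marker term. Whether a marker changes the TENS effect requires the pain outcome as the response, with arm, marker and arm × marker as predictors.

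**Step 4. Does the sample size change?** No. The plan's chain is 42 per group; 42 / 0.85 = 49.4, rounded up to 50; 2 × 50 = 100; 100 × 1.20 = 120. No marker enters it.

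**Step 5. What would adding PPT cost in multiplicity?** Take TS and DNIC as one variable each, one test per marker on one outcome at the stated 0.05, and independent tests (all assumptions). The chance of at least one nominal positive when nothing is there is:

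- two markers: 1 − 0.95² = 0.0975, about 10%;
- four markers (adding knee and arm PPT): 1 − 0.95⁴ = 0.185, about 19%.

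With four outcomes the number of tests per time point rises from 2 × 4 = 8 to 4 × 4 = 16.

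**The case against.** The strongest reply is that the aim section is the outlier. The Background reports that central sensitization in knee osteoarthritis was detected by enhanced TS and impaired DNIC. The measurement section, the regression and the Discussion all follow that, and the Discussion speaks of components rather than of central sensitization as a whole. The aim section lists measures and does not offer a definition. PPT data are collected in any case, so nothing is lost, and the analysis is secondary.

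Much of this stands. It makes the second repair below (narrowing the aim) a legitimate one, and it keeps the point minor. It does not make the sections agree: the aim still names PPT as a measure of central sensitization.

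Three stronger readings are tempting, and the documents do not support them:

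- *That the second aim is otherwise properly tested and lacks only PPT.* Step 3 shows that the regression as worded would not test it with or without PPT.
- *That the omission costs a known amount of power.* Any such figure needs an assumed size of effect modification, an assumption that it acts through PPT, and an assumed correlation of PPT with TS and DNIC. The protocol gives none of these, and the opposite assumptions would make PPT the weak marker.
- *That scaling the stimulus removes the threshold from TS and DNIC almost entirely, or that arm PPT is the feature from which an adverse TENS effect is predicted.* The first has no figure behind it. On the second, the Background lists many kinds of stimulus and bases its prediction on electrical stimulation of A-beta fibres.

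**Conclusion.** The inconsistency is real and stands in the current text. PPT at the knee and arm is a named measure of central sensitization in the aim and a listed baseline variable, yet it is absent from the section on detecting central sensitization, from both analysis lists and from the restated aim. As written, a conclusion about central sensitization would be wider than the markers examined.

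The point is minor. It concerns an exploratory secondary analysis, needs no new data, and leaves the primary comparison and the sample size as they are. The conclusion rests on comparing the sections and on the stated TS and DNIC procedure, not on any assumed effect size.

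**What to change.** Reconcile *Aim of the proposed study*, *Central sensitization*, *Data reduction and Statistical analysis* and *Discussion* before results are seen, in one of two ways.

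1. **Keep PPT.** Name baseline knee PPT and arm PPT with TS and DNIC as exploratory markers for the second aim. Analyse each as a predictor of the pain outcome, in a model with treatment arm, the marker and an arm-by-marker term. Report the results marker by marker and label them exploratory.
2. **Drop PPT as a marker.** Remove it from the assessment of central sensitization in the aim, keep it as the calibration for TS, and limit the conclusion to TS and DNIC. The regression still needs its response and predictors put the right way round and a treatment term added.

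The second way costs wording only. The first adds two markers from data already collected, and so more nominal tests at 0.05, as worked out above; marker-by-marker exploratory reporting makes that visible but does not remove it.

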## Abstract

**Background:**

Central sensitization has recently been documented in patients with knee osteoarthritis (OAk). So far, the presence of central sensitization has not been considered as a confounding factor in studies assessing the pain inhibitory effect of tens on osteoarthritis of the knee. The purpose of this study is to explore the pain inhibitory effect of burst tens in OAk patients and to explore the prognostic value of central sensitization on the pain inhibitory effect of tens in OAk patients.

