### Sensitization in relation to the effect of tens

The effectiveness of tens on knee pain in OAk patients is unclear, due to conflicting results [13]. The ambiguous results of the included studies could be due to the inclusion of heterogeneous types of patients. One important feature distinguishing patient groups might be the presence of central sensitization.

In case of central sensitization, the response to peripheral stimuli, e.g., electrical stimuli as well as mechanical pressure, cold, heat, light, sound and chemical substances is enhanced [26]. Tens (Burst) currents influence pain through the electrical stimulation of low-threshold A-beta cutaneous fibers. This stimulation might enhance the responsiveness of central pain-signaling neurons of OAk patients who are centrally sensitized. In these patients an adverse effect of tens on the pain perception can be expected. The identification of potential subgroups of sensitized and non-sensitized symptomatic OAk patients is needed, as they can react differently to tens. So far, the presence of central sensitization has not been considered as a confounding factor in studies assessing the pain inhibitory effect of burst tens on OAk.

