#### Secondary outcome variables

The change from baseline to final assessment of the study knee in *self-reported knee pain and difficulty with physical function *will be measured using the WOMAC Index [32].

The *global perceived effect *(GPE) compared to baseline will be measured on an ordinal scale (1 - much worse, 2 - slightly worse, 3 - no change, 4 - slightly better, 5 - much better) [35]. The GPE is an overall measurement of the perceived effect of the patient. It has been used in various studies to assess therapeutic effects [36-38].

The change from baseline to final assessment of *medication use *will be recorded as another pain variable.

*Pressure pain threshold, temporal summation (TS) and *Diffuse noxious inhibition control (DNIC) will be used as baseline variables.

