## Discussion

This study has a double aim. First, to explore the pain inhibitory effect of tens in OAk patients. Second, to assess whether components of central sensitization like temporal summation and diffuse noxious inhibitory control, affect this pain inhibitory effect.

It is believed that tens influences pain through different pathways. One of these pathways is the gate-control theory [9]. The second goal of our study protocol, i.e. exploring the potential prognostic value of TS and DNIC on the pain inhibitory effect of tens, is based on this rationale. However, opioid pathways that involve peripheral, spinal and supraspinal mechanisms [41,42] are also proposed as an explanation for the pain modulation of tens and this pathway may be less vulnerable for an adverse effect of tens in central sensitized OAk patients.

As tens may influence pain through the electrical stimulation of low-threshold A-beta cutaneous fibers, the responsiveness of central pain-signaling neurons of OAk patients who are centrally sensitized is augmented to the input of these electrical stimuli. This would encompass an adverse therapy effect of tens on the pain perception in patients with OAk who are centrally sensitized. Therefore we think that it might be interesting to identify a subgroup of symptomatic OAk patients, i.e., non-sensitized patients, who are likely to benefit from burst tens.

The majority of studies that were published in the past and that focused on treatment effects of tens, embody currents that were administered by a therapist in a practice or hospital setting. As portable tens devices are marketed as small, inexpensive, easy-to-use home units [13], we choose to use a self-administered protocol. This approach may encompass a positive influence on the patient's participation to the treatment as well as to the cost effectiveness of the treatment, as the machines that are used in (professional) practices are far more expensive than these portable tens devices.

To assess whether dose-effects may influence the treatment outcome, we plan to record the daily duration of the electro stimulation that is applied.

One major concern when using self-administered medical care is treatment adherence. We think that a weekly phone call after the initial start of the study may improve treatment adherence as well as stimulate participants to consistently fill out the diary.

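### The secondary regression swaps outcomes and predictors and has no treatment-by-marker term, so no stated analysis answers the second aim

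*Protocol article*

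**What the plan says.** The second aim appears three times in the protocol article.

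- Abstract, Background: "to explore the prognostic value of central sensitization on the pain inhibitory effect of tens in OAk patients".
- Aim of the proposed study: "Second, to assess whether central sensitization affects this pain inhibitory effect".
- Discussion: "exploring the potential prognostic value of TS and DNIC on the pain inhibitory effect of tens".

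The section on sensitization and the effect of TENS gives the reason. Identifying "subgroups of sensitized and non-sensitized symptomatic OAk patients is needed, as they can react differently to tens", and an adverse response is expected in sensitized patients.

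The outcome sections fix the roles of the variables. The primary outcome is "The change from baseline to final assessment of the study knee in the continuous variables" KPa and KPp. WOMAC pain and function are secondary outcomes, also as change. Pressure pain threshold (PPT), TS and DNIC "will be used as baseline variables".

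The statistical section then names two analyses. The first is a repeated measures ANOVA comparing the arms at 6 and 12 weeks, with age and sex as the only possible covariates. The second is the secondary regression: "a linear regression analysis will be used with the following dependent factors: BMI, TS and DNIC; and as independent factors: KPa, KPp, WOMAC subscales".

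**The concern.** The aim concerns a difference between arms that varies with a baseline marker. The model that should address it has the marker as the response and the pain scores as predictors, makes BMI an outcome, and leaves treatment out. Followed as written, it pools TENS and sham, and effect modification is not one of its parameters.

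At stake is the subgroup conclusion that the Abstract and Discussion look forward to, namely that non-sensitized patients are the ones likely to benefit. A pooled association could be presented as evidence for that conclusion when it shows only that more sensitized patients have more pain, or improve less, whatever they receive.

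**Working it through.** **1. Roles of the variables, side by side**

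| Variable | Outcome sections | Secondary regression |
|---|---|---|
| KPa, KPp | primary outcomes (change) | independent |
| WOMAC pain, function | secondary outcomes (change) | independent |
| TS, DNIC | baseline variables | dependent |
| BMI | baseline characteristic | dependent |
| Treatment arm | randomized factor | not listed |
| Treatment x marker | implied by the second aim | not listed |

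The ANOVA contains treatment but no marker. The regression contains markers but no treatment. Neither contains both, so no stated analysis tests the second aim.

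**2. What swapping the sides back would achieve**

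The model would become pain = a + b x TS, over both arms together. Here b measures whether TS goes with pain. The second aim needs d in

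pain = a + c x treatment + b x TS + d x (treatment x TS).

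With one predictor, the test of b is the same whichever variable is called dependent. The reversal alone therefore does not change that test. The missing treatment and interaction terms are the substantive gap.

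**3. How often a purely prognostic marker would look like a finding**

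Inputs:
- N = 120 x 0.85 = 102 evaluable patients (Sample size section: 120 recruited, 15% loss).
- Two-sided alpha 0.05.
- Marker-pain correlation r. The article gives none, so 0.1 to 0.3 is an assumed range.
- No effect modification and no main effect of treatment.

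Power of the pooled test is approximately Phi(atanh(r) x sqrt(N - 3) - 1.96), where sqrt(99) = 9.950.

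| r | atanh(r) x 9.950 | Pooled regression significant | Interaction test |
|---|---|---|---|
| 0.1 | 0.998 | 17% | about 5% |
| 0.2 | 2.017 | 52% | about 5% |
| 0.3 | 3.080 | 87% | about 5% |

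Simulation with 51 patients per arm agrees. It gives 16-17%, 50-53% and 84-88%, depending on whether 0.1 to 0.3 is read as a correlation or as a slope with residual SD 1. These are one-predictor figures. The article lists four overlapping pain and function scores.

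**4. When modification is truly present**

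Simulated with N = 102, residual SD 1 and assumed slopes per marker SD:

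| Sham slope | TENS slope | Pooled significant | Interaction test |
|---|---|---|---|
| -0.35 | +0.35 | about 6% | about 93% |
| 0 | 0.70 | about 87% | about 93% |
| 0 | 0.35 | about 40% | about 40% |

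The pooled model misses modification mainly when the slopes in the two arms cancel. Otherwise it often gives a signal but cannot say whether the signal belongs to TENS.

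**5. Precision of the interaction**

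The plan's main sample size reproduces: 2 x (4.7 x (1.96 + 0.84) / 2.9)^2 = 41.2, so 42 per group; 42/0.85 gives 50; and 50 x 1.2 x 2 = 120. It is sized for the main comparison only.

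For a continuous marker, the interaction detectable at 80% power is 2.8 x SD / sqrt(N x 0.25), per SD of marker:
- SD 4.7 (Sample size section): 2.8 x 4.7 / sqrt(25.5) = 2.6 points.
- SD 2.5 (assumed): 2.8 x 2.5 / sqrt(25.5) = 1.4 points.

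**The case against.** **It may be only a slip of wording.** That is likely for the labels, since the outcome sections give the right roles. A reader might infer that the reversal by itself invalidates the test, but in the one-predictor case it makes no difference. Correcting the labels, however, leaves treatment and the interaction out.

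**Prognostic value may need only a main effect.** The article attaches the phrase each time to the pain-inhibiting effect of TENS, and the aim asks whether sensitization affects it. That effect is defined only against sham.

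**An analysis plan may hold the right model.** It may, and silence in the article would not be a finding. Here the article states a model with explicit variable lists that conflict with its own outcome sections and aim. That sentence needs correcting whatever another document says.

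**The harm can be overstated.** This stands. A reader might infer that the pooled model would usually miss real modification, citing 6% against 93%. Those figures need exactly opposite slopes in the two arms. The article expects an adverse response to TENS in sensitized patients and gives no reason for an opposite slope under sham. With a flat sham slope the contrast is 87% against 93%. That 93% also flatters the remedy: an interaction of 0.70 SD is 0.70 x 4.7 = 3.3 points, more than the whole assumed treatment effect of 2.9.

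**PPT.** A reader might treat its absence from the regression as a further error, because the aim section says "we aim to assess the central sensitization by measuring pressure pain thresholds (PPT) at the knee (local pain) and at the upper limb". The Central sensitization section and the Discussion name only TS and DNIC for this purpose, so the point is weak.

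**Conclusion.** The point holds. The stated regression contradicts the article's own variable roles, and no stated analysis contains both treatment and a sensitization marker, so a declared aim cannot be answered as planned. This conclusion rests on the text alone and on no numerical assumption.

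The main fault is attribution. A significant pooled association may be prognostic only, and nothing in the model can credit it to TENS. How often that would mislead depends on an unknown correlation: from about 17% of trials at 0.1 to about 87% at 0.3, for 102 evaluable patients and no true modification. These are illustrations, not figures from the article.

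The article labels this a secondary analysis. The primary comparison of TENS with sham is not affected.

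**What to change.** Replace the regression sentence with a linear (mixed) model along these lines:

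- **Dependent variable:** follow-up KPa or KPp, and likewise WOMAC pain and function.
- **Independent terms:** treatment, baseline value of that outcome, baseline TS or DNIC as a continuous variable, treatment x marker, age, sex and BMI.
- **Markers:** one per model, baseline values only. TS and DNIC are measured again at 6 and 12 weeks, and those values could themselves be affected by treatment.
- **Multiplicity:** name one lead marker and one lead outcome. Two markers by four outcomes already gives 8 interaction tests, and 12 with PPT. Treat the others, including PPT if used, as supportive.
- **Reporting:** the interaction estimate with its 95% CI, labelled exploratory.

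The cost is wording only, since every variable is already collected. The drawback is low precision: at 80% power only an interaction of about 2.6 points per marker SD is detectable at SD 4.7, or about 1.4 if the SD is 2.5. A non-significant interaction should therefore not be read as showing that sensitization is irrelevant.
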